## Abstract

**Objectives:**

This study aims to analyze the effectiveness of adding inspiratory muscle training (IMT) to a cardiac rehabilitation program (CRP) in people with acute myocardial infarction (AMI) revascularized by percutaneous coronary intervention (PCI) after 16 sessions. The biopsychosocial profile and the sex differences of this population will also be evaluated.

**Design:**

Triple-blind, parallel-group, low-risk randomized controlled trial.

**Methods:**

72 patients diagnosed with AMI will be enrolled and randomly assigned to two groups. The control group will complete the usual CRP with the addition of IMT at 5% of the maximal inspiratory pressure (MIP) (sham load). The intervention group will perform the same CRP but will add an IMT program at 70% of MIP. Outcomes will be collected at baseline and post-intervention. The main outcome will be cardiorespiratory fitness (CF) measured in metabolic equivalent of task (MET), secondary outcomes will be MIP, maximal expiratory pressure, peripheral muscle strength, dyspnea, social support, anxiety, depression, coping with the disease, sexual dysfunction, quality of life (QoL), sleep quality, eating habits, and body composition. Descriptive statistics will summarize baseline data, and influential outliers will be managed via winsorization or exclusion, confirmed by sensitivity analyses. A mixed-design ANOVA will evaluate differential changes over time. Depending on attrition rates, missing data will be addressed using either complete case analysis (<5%) or multiple imputation with an intention-to-treat approach (>5%).

**Discussion:**

According to recent literature, improvements in CF and MIP are expected. For the rest of the outcomes, data are currently limited, inconclusive or lacking. We hypothesize that changes in CF may affect the rest of the outcomes and, in our opinion, IMT at 70% of the MIP will significantly improve CF.

**Clinical implications:**

If the expected benefits are observed, the results may recommend including IMT as a fundamental component of a CRP in our study population.

**Trial registration number:**

Registered prospectively at ClinicalTrials.gov (NCT06681740) Version 4.

## Introduction

Acute myocardial infarction (AMI) is characterized by narrowing of the internal lumen of the arteries that perfuse the heart. As the arterial lumen narrows, blood flow decreases, consequently diminishing the oxygen supply to the myocardium. This condition may lead to angina pectoris or may potentially result in acute myocardial infarction [1–3]. It is the leading cause of death from cardiovascular disease and is responsible for 9.44 million deaths in 2021 and 185 million disability-adjusted life years [4]. Therefore, it is one of the most important public health problems worldwide, and entail a high health and social spending [5]. In that way, percutaneous coronary intervention (PCI) is one of the most common treatments for AMI because it is a minimally invasive technique [6]. In addition to this surgical technique to revascularize the myocardium, it is necessary to prevent further cardiovascular events. Cardiac rehabilitation programs (CRPs) are widely recognized as effective non-pharmacological interventions for improving the quality of life (QoL) and preventing subsequent cardiovascular events in patients with AMI [7–10]. For these and other reasons, CRPs are recommended as an essential intervention after coronary events in the clinical practice guidelines of major international associations such as the European Society of Cardiology [11], the American Heart Association and the American Association of Cardiovascular and Pulmonary Rehabilitation [12]. These include smoking cessation, control of other cardiovascular risk factors, health education, psychological therapy, and multimodal exercise programs [13–16]. Two types of exercise are usually performed: endurance and strength training [12]. The third type of exercise is inspiratory muscle training (IMT), which is widely used in patients with heart failure (HF) [17]. This involves applying higher-than-usual workloads to the muscles responsible for generating the necessary negative pressure inside the thorax for air to enter the lungs. This overload induces adaptations that increase the muscle strength. It is a safe intervention that reduces dyspnea and improves cardiorespiratory fitness (CF) and QoL in these patients [18]. In that sense, a recent systematic review with meta-analysis by Fabero-Garrido et al. [16] concluded that the quality of the evidence for the use of IMT to improve maximal oxygen consumption and expiratory muscle strength in people who suffer from ischemic heart disease is very low. Therefore, the available literature analyzing the effectiveness of IMT in people with AMI who underwent revascularization by PCI is limited. Consequently, it is pertinent to conduct a low-risk randomized clinical trial to evaluate the effectiveness of adding IMT to a CRP in this specific group.

The primary aim of the proposed study is to analyze the effectiveness of adding IMT to a CRP in people with AMI who underwent revascularization by PCI after 16 intervention sessions (2 times/week), based on CF, maximal inspiratory pressure (MIP), maximal expiratory pressure (MEP), peripheral muscle strength, social support, anxiety, depression, coping with the disease, sexual dysfunction, QoL, sleep quality, eating habits, and body composition.

As a secondary aim, we will determine the biopsychosocial profile and analyze sex differences in this population through subgroup analyses.

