### Sample size calculation

The sample size was calculated to detect differences between groups in our main outcome, CF, measured by VO_2_max. According to the meta-analysis by Fabero-Garrido et al [16], people with ischemic heart disease who have undergone an IMT program have a mean difference of 2.18 ml O_2_/kg/min with respect to the control group, and we want to find a deviation of 1 MET (3.5 ml O_2_/kg/min). The calculations were performed using the statistical software G*Power 3.1, considering a confidence level of 95% and a power of 80% in all cases.

Based on the above, a sample size of 33 subjects per group (66 in total) was determined. In addition, to minimize the impact of possible dropouts, the total sample was increased by 10% to 72 patients, which will lead to the final inclusion of 36 patients in each group.

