### Statistical analysis

Descriptive statistics will summarize each variable, reporting means ± standard deviations (SD) or medians (IQR) for continuous data and absolute and relative frequencies for categorical data to verify baseline comparability between groups. Exploratory data analysis (e.g., box-plots, z-scores) will screen for influential outliers; values deemed spurious will be winsorized or, when justified, excluded, and sensitivity analyses will confirm that their treatment does not alter the main findings.

A mixed-design analysis of variance (ANOVA) will be performed to assess differential changes between groups over time (group × time interaction). The primary analysis strategy will depend on the proportion of missing data: if the dropout rate is less than 5%, a complete case analysis will be conducted, as this threshold is generally considered to have a negligible impact on bias. However, if missing data exceeds 5%, an intent-to-treat approach will be implemented, using multiple imputation to handle missing values and ensure that all randomized participants are included in the final model, in accordance with clinical trial standards [42].

All analyses will be performed in IBM SPSS Statistics v.24 (IBM Corp., Armonk, NY, USA), significance level will be set at 5% with 95% confidence intervals; assumptions, model fit, and potential risks (e.g., heteroscedasticity or multicollinearity) will be routinely checked, and predefined contingency strategies (nonparametric alternatives or robust estimators) will be implemented when violations are detected.

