## Discussion

The present study will analyze the effect of adding IMT to a CRP in people with AMI who underwent revascularization by PCI. It is expected that CF and MIP will improve because there is some evidence (low and moderate) of this, as concluded in a recent review with meta-analysis by Fabero-Garrido et al. [16]. Furthermore, in similar clinical populations such as patients with HF, there is a high level of evidence that these outcomes and QoL, improve [18]. Therefore, it can be expected that the results are similar in AMI, in spite of no improvements in QoL have been evidenced yet in PCI patients. Nor have significant gains in sleep quality been observed to date, according to the available studies. In those variables without prior evidence, such as peripheral muscle strength, social support, anxiety, depression, coping with the disease, sexual dysfunction, eating habits, and body composition, we hypothesize that there will be an improvement, since increasing CF will reduce dyspnea during daily activities and thus could contribute, in our opinion, to the enhancement of other aspects of the individual. We decided to perform IMT at 70% of MIP based on a recent meta-analysis by Azambuja et al. [18]. As they concluded, training at loads above 60% of MIP had greater increases in inspiratory muscle strength, CF, and QoL in patients with HF. We expect these greater effects to occur in people with AMI as well. In the case of CF, our main outcome, the improvement occurs for three reasons. First, early inspiratory muscle fatigue is delayed because it induces metaboloreflex which decreases blood flow to the peripheral musculature [43–46]. Second, blood supply to the peripheral musculature is increased by decreasing the blood demand of the inspiratory musculature [47–49]. Thirdly, IMT can reduce the peripheral chemoreflex response and enhance heart function. This is directly linked to decreased sympathetic activity in individuals with HF, leading to better systemic vasodilation, improved blood flow to peripheral muscles, greater ventilatory efficiency, and, as a result, increased CF [50]. Although undertaking a CRP itself improves psychosocial outcomes, dedicated IMT has further reduced fatigue, depression and perceived dyspnoea in patients with stable angina [51] and HF [52]. IMT has also demonstrated improvements in the psychosocial domain in healthy people [53] and people with chronic obstructive pulmonary disease [54,55]. Improved breathing efficiency may decrease the cognitive load associated with exertional breathlessness, fostering greater self-efficacy, exercise adherence and ultimately enhanced QoL. Women remain under-represented in cardiac rehabilitation (CR) trials, and it is a relevant aspect for the individualization of a CRP [56]. From a physiological perspective, women have lower respiratory muscle mass and lower basal MIP than men [57], which may predispose them to relatively greater improvements after IMT. Emerging evidence suggested that female patients obtain smaller absolute but similar relative gains from a CRP [58]. Therefore, our results will allow us to explore effect modification by sex, which may inform personalized prescriptions and help close the persistent gender gap in CR outcomes.

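### The sex-difference aim names subgroup analyses, but the effect modification that the Discussion wants to explore needs a treatment-by-sex term, and none is named

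*Protocol article*

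**What the plan says.** Three places in the protocol article bear on this.

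- Introduction, last paragraph (aims): the secondary aim is to describe the biopsychosocial profile and to "analyze sex differences in this population through subgroup analyses".
- Discussion: after remarks on women's lower baseline inspiratory pressure and their under-representation in cardiac rehabilitation trials, the article says that "our results will allow us to explore effect modification by sex, which may inform personalized prescriptions".
- Statistical analysis: the model is a mixed-design ANOVA, used to "assess differential changes between groups over time (group × time interaction". No sex factor is named. On error rates the section says that the "significance level will be set at 5% with 95% confidence intervals".

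The expected number of women is not given. Allocation is by simple randomisation (Allocation concealment), so the arms are not balanced within sex by design.

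**The concern.** The question in the Discussion is whether the training effect differs between men and women. That is one quantity, the effect in men minus the effect in women, with its own standard error. An analysis in each subgroup gives two effects and two p-values. Seeing that one p-value is below 5% and the other is not is no test of the difference. Two subgroups with the same true effect often fall on opposite sides of the threshold, because each has much less power than the whole trial.

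With fewer women than men, such a disagreement usually takes the form of a significant result in men only. It could be read as evidence that inspiratory muscle training does not help women, although the aim is to serve women better.

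**Working it through.** **Inputs from the article.** 33 per arm, 66 in total, raised to 72 for dropout; "considering a confidence level of 95% and a power of 80% in all cases" (Sample size calculation); 5% level; 1:1 allocation. Two effect figures appear there: 2.18 ml O2/kg/min from the cited meta-analysis, and 3.5 ml O2/kg/min, introduced by "we want to find a deviation of 1 MET".

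**Inputs assumed.** No SD is stated, so the standardised effect d has to be bracketed. The share of women is not stated; I use 20%, 30% and 50%. The same d is taken as true in both sexes.

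**Reproducing 33 per arm.** Two readings of the sample-size text lead there (noncentral t).
- Two-sided 5%, 80% power, 33 per arm requires d = 0.70. With a target of 3.5 this implies an SD of 3.5/0.70 = 5.0.
- If 3.5 is read as the SD, d = 2.18/3.5 = 0.62. At one-sided 5% the power is 79.4% with 32 per arm and 80.5% with 33, so 33 is needed. At two-sided 5% the power with 33 is 70%.

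A third value, d = 2.18/5.0 = 0.44, covers the meta-analysis effect with the SD from the first reading. The range is therefore 0.44 to 0.70.

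**Method.** With two time points, the group × time test equals a two-sample t test on change, so d is in SD units of change. For n per arm within one sex:
- power P = Pr(|t'| > t(0.975, 2n − 2)), where t' is noncentral t with parameter d·√(n/2);
- the sexes are separate patients, so Pr(tests disagree) = Pw(1 − Pm) + Pm(1 − Pw);
- Pr(significant in men only) = Pm(1 − Pw);
- the treatment-by-sex term has standard error √(2/nw + 2/nm) in SD units, with N − 4 = 62 degrees of freedom.

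**Results, N = 66, two-sided 5%, identical true effect in both sexes.** The last column instead takes a true sex difference equal to d.

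| d | women/men per arm | power in women | power in men | tests disagree | men only | interaction power for a difference of d |
|---|---|---|---|---|---|---|
| 0.44 | 7/26 | 12% | 34% | 38% | 30% | 11% |
| 0.44 | 10/23 | 15% | 31% | 37% | 26% | 13% |
| 0.44 | 16/17 | 23% | 24% | 36% | 18% | 14% |
| 0.62 | 7/26 | 19% | 59% | 56% | 48% | 17% |
| 0.62 | 10/23 | 26% | 54% | 52% | 40% | 21% |
| 0.62 | 16/17 | 40% | 42% | 48% | 25% | 24% |
| 0.70 | 7/26 | 23% | 70% | 61% | 54% | 21% |
| 0.70 | 10/23 | 32% | 64% | 55% | 44% | 25% |
| 0.70 | 16/17 | 48% | 51% | 50% | 26% | 29% |

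Worked line (d = 0.70, 7/26): 0.226 × (1 − 0.697) + 0.697 × (1 − 0.226) = 0.068 + 0.539 = 0.61. A simulation of 40,000 trials gave 60.8% disagreement, 54.1% significant in men only, and 5.05% false positives for the interaction test. An unrounded 6.6 women per arm moves the upper ends to 62% and 55%.

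**No true effect in either sex.** Disagreement is 2 × 0.05 × 0.95 = 9.5%.

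**Precision of the interaction.** The standard error is √(2/7 + 2/26) = 0.602 SD with 7 women per arm and √(2/10 + 2/23) = 0.536 with 10. For the main effect it is √(2/33) = 0.246. The ratio is 2.4 and 2.2. The sex difference detectable with 80% power is about 1.7 and 1.5 SD.

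**The case against.** The strongest reply is that the article does not commit to separate tests. Subgroup analysis is a general label that can include an interaction test, and nothing in the text rules one out. The full protocol or an SAP, neither of them shown, may specify it. A condensed article need not set out the model for a secondary aim, so the missing sex term alone would be no finding. All of this stands. A reader might infer that the plan is to test men and women separately and compare p-values; the text does not say so. What remains is that the method the article names does not by itself deliver the inference it draws.

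The aims sentence can also be read as a descriptive comparison of men's and women's profiles. In part it is, and that needs no interaction. But "our results will allow us to explore effect modification by sex" shows that the treatment effect is in view too.

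Three further inferences would go too far.
- That few women cause the disagreement. With near-equal numbers it is still 36% to 50%. Imbalance adds somewhat and mainly sets the direction.
- That a men-only result is the likely outcome. It arises in 26% to 54% of trials with 20% to 30% women, passes half only at the top of the range, and presupposes a real effect.
- That the Discussion promises personalised prescribing. Its wording is already cautious: it speaks of exploring, and of what the results might inform.

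Finally, the interaction test has little power here. That is true, and it is why an estimate with an interval is asked for and not a verdict.

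**Conclusion.** The point holds as a mismatch between named method and stated inference. If the subgroup analyses are the group × time ANOVA run within each sex, an identical true effect produces conflicting significance in about 36% to 61% of trials, against 5% for the interaction test. These figures rest on an assumed d of 0.44 to 0.70, an assumed 20% to 50% women and 66 analysed patients. The conclusion does not depend on the share of women, but it does depend on there being a real effect, since without one the figure is 9.5%. Whatever the method, a trial of this size has only about 11% to 25% power, with 20% to 30% women, for a sex difference as large as the whole treatment effect, so any finding on sex is hypothesis-generating. The aim is secondary, and the primary analysis and sample size are untouched.

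**What to change.** - Introduction (aims): state that effect modification by sex will be assessed by a treatment-by-sex term. The descriptive comparison of men's and women's profiles can stay as it is.
- Statistical analysis: add that term, as group × time × sex in the planned mixed ANOVA. Report the difference in effect between the sexes with its 95% confidence interval, labelled exploratory. Take the sex-specific effects from the same model and make no significance claim within one sex. Fit this as a second model, because adding the three-way term changes what the group × time row estimates; the primary analysis then stays as written.
- Discussion: add that power for a sex difference as large as the whole treatment effect is about 11% to 25% under the assumptions above, so the result is hypothesis-generating.

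The cost is one extra model term and a few sentences. Sex is already recorded, so recruitment and data collection do not change. If an SAP already specifies the interaction, only the article's wording needs aligning.

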## Materials and methods

### Design

An 8-week, triple-blind, parallel-group, low-risk, randomized controlled trial (RCT) will be conducted in patients with AMI who underwent revascularization by PCI. This protocol was reported according to the Standard Protocol Items: Recommendations for Interventional Trials (SPIRIT 2013 Statements) [19]. The checklist is available in the supporting information (S1 File). Furthermore, the Consensus on Exercise Reporting Template (CERT) has been included as Supporting Information (S6 File) to provide comprehensive rehabilitation details and guarantee the intervention's replicability.

### Participants and the study setting

This study will include patients with AMI who underwent revascularization by PCI. These individuals will be recruited from among patients admitted to a CRP in the Cardiac Rehabilitation Unit (CRU) of the Hospital Universitario Virgen de la Victoria in Málaga (HUVV), Spain. Physicians in charge of potential participants with AMI who underwent revascularization by PCI will propose inclusion in the study by applying the eligibility criteria. The recruitment began on November 11, 2024, and will end on December 31, 2025. Patients will receive general information and written consent forms from their doctors, who will ask them about their interest in participating in the RCT. If the answer is yes, they will be asked to sign the written informed consent form. This will be kept in a safe place by the researchers.

### Eligibility criteria

The inclusion criteria will be as follows: a) male and female patients with AMI who underwent emergency revascularization by PCI aged over 18 and under 80 years, and b) with absence of cognitive deficits and/or physical limitations that would prevent them from performing physical exercise or completing the questionnaires necessary for participation in the study. Patients will be excluded if they have undergone revascularization via coronary artery bypass grafting or if they present with one of the main absolute contraindications for initiating cardiac rehabilitation in patients with AMI: unstable angina, decompensated heart failure, severe uncontrolled arrhythmias, severe uncontrolled hypertension, and acute myocarditis or pericarditis [20].

### Interventions

Both study groups will undergo 16 intervention sessions (2 times/week) of a CRP, consisting of multicomponent exercise (endurance and strength training), health education, and weekly group psychological therapy sessions. This program includes the core components of CRPs recommended by the American Heart Association and the American Association of Cardiovascular and Pulmonary Rehabilitation [12].

The CRP will be performed and supervised by the usual multidisciplinary team of the HUVV. The team is composed of a cardiologist, rehabilitation physician, endocrinologist, physiotherapist, nurse, and psychologist. The study participants will attend the CRU of the hospital three times per week. Two of these days will be dedicated to physical exercise sessions, and the third will be dedicated to health education and group psychological therapy sessions. The health education session will deal with a different topic each week (basic knowledge of their pathology, proper medication, safe physical exercise, sexual dysfunction, healthy eating, and control of cardiovascular risk factors). Subjects suffering from erectile dysfunction will be offered the possibility of being referred to a urologist. Participants with poorly controlled diabetes and/or morbid obesity will be referred to an endocrinologist on the CRU.

The training sessions will take place in the cardiac rehabilitation room at the HUVV in groups of 8 patients and will last approximately 75 minutes. This space has a rectangular floor plan, measures approximately 100m^2^, and is air-conditioned. It contains the equipment described in Table 1 for conducting exercise sessions, as well as telemetry equipment for monitoring participants during exercise. In addition, it has everything necessary to respond in the event of any adverse effects or cardiopulmonary arrest. This includes a stretcher, wheelchair, sphygmomanometer, stethoscope, electrocardiograph, and a fully equipped crash cart with a defibrillator.

**Table 1 pone.0343947.t001:** Structure of the cardiac rehabilitation exercise session.

Category	Description
Patient reception	Collection of constants (blood pressure, heart rate, and glycemia in case of diabetic patients), and placement of telemetry.
Warm-up	A battery of different full body exercises will be performed including diaphragmatic breathing, balance exercises, low load strength exercises and gentle endurance exercises.
Strength Exercise	It will consist of different exercises with dumbbells and elastic bands involving various joints. Participants will work at 50% of their 1 repetition maximum (1RM), measured indirectly using the 20 repetitions maximum (20RM) method. Three sets of 10 repetitions of the following exercises will be completed: elbow flexion, shoulder abduction and knee extension. The rest interval between sets will be 30 seconds.
Endurance Exercise	It will be performed on a treadmill or stationary bicycle. The duration of the training will be 30 minutes. In the first month, each patient will be trained at 70% of their heart rate resulting from applying the Karvonen formula, and in the second month, at 80%. The modality may be continuous or intervallic, depending on the patient's tolerance.
Relaxation and calm-down	Patients will remain seated in chairs for 5 min, during which a guided relaxation audio will be played in order to facilitate the return of their heart rates and blood pressures to baseline values
End of session and farewell	Vital signs will be checked to ensure that participants are leaving in appropriate condition. They will be given advice on healthy lifestyle habits before their departure.

The training sessions will be led by a physiotherapist with previous experience and training in supervising exercise for people with heart disease. This professional will keep an attendance record on the computer in order to measure and report adherence. In addition, this physiotherapist will encourage patients in each session to continue with the program by reinforcing its benefits. The structure and other details of the sessions are shown in Table 1.

The program will be extended for eight weeks until 16 concurrent training sessions are completed.

In addition to the classic CRP described above, the intervention group will undergo IMT during the same period. The Power Breath model – Medic Classic device will be used. The IMT will be performed by adjusting the device load to 70% of the MIP value measured prior to the start of the program. Participants will complete one daily training session four days a week (Monday, Wednesday, Friday, and Sunday), three sets of 10 repetitions, and a rest of 3-minutes between sets. The MIP value will be measured again halfway through the program to readjust the training load. Previous studies with patients with coronary artery disease have used training protocols that are similar in terms of workload, number of repetitions and sets, and distribution of weekly sessions. These clinical trials reported no adverse events, supporting the safety and tolerability of high-intensity IMT in this study population [22–24]. We hypothesize that high-intensity IMT training may lead to greater inspiratory muscle adaptations, resulting in improved CF and other outcomes compared to lower-intensity training [21–23].

The control group will be given the same device as the experimental group, but the load for all participants in the control group will be 5 cm of H_2_O. This load is so low that it cannot induce improvements in the inspiratory musculature. Therefore, it will act as a sham intervention in the control group.

A rehabilitation physician, with prior expertise and training in the practice of the device, will teach participants how to use it on the first day, and they will be instructed to do it individually at home. In order to prevent non-compliance with the IMT by the participants, they will be given a paper log to be filled in daily after the IMT session. At any time, participants may ask the rehabilitation physician who instructed them any questions they may have about using the device. During regular CRP exercise sessions, the physiotherapist will emphasize the importance of completing the prescribed IMT.

